#### Safety assessment

Laboratory tests and ECGs will be performed for safety outcomes. Blood levels of AST/ALT, glucose, BUN, Cr, Na, K, Cl, cholesterol, LDH, and CPK will be measured at baseline, 12, and 24 weeks after medication. An ECG will be performed at baseline, and 24 weeks after medication. Vital signs will be recorded at every visit. Any abnormal results in laboratory tests, ECG or vital signs, will be closely monitored. The investigators will call participants by phone 4 weeks after completion of medication, to monitor occurrence of any adverse events.

### Data management and monitoring

Case report forms (CRFs) will be used for each participant to collect relevant data. To promote data quality and accuracy, one trained investigator will complete the CRFs and a second investigator will independently review all CRFs. All documents will be kept at the study site, and the data will be entered and stored in a password-protected computer. All procedures will comply with confidentiality standards for medical data. All documents and collected data will be kept for 3 years after completion of the study, and will then be destroyed. The data management process will be monitored by an independent agent. Only the investigators and the monitoring agent will have access to the dataset. Auditing will be conducted by the Korean Ministry of Food and Drug Safety.

### Statistics

#### Sample size calculation

This clinical trial is a pilot study to examine the feasibility of a full randomized clinical trial of KGT, and to determine the sample magnitude required for large-scale studies. To our knowledge, no prior study has investigated the effect of KGT on MCI. There are no previous data indicating the sample size needed to yield statistically significant results for determining the effect of KGT by the SNSB scores. For pilot trials, the sample size of 10–20 participants per group was suggested by Kieser and Wassmer. [13]. Browne recommended using at least 30 subjects to estimate parameters [14]. Our target sample size is 30, so 38 individuals will be recruited to allow for a 20% dropout rate.

#### Data analyses

The investigators, along with an independent professional statistician, will perform the data analyses. All statistical analyses will be performed using SPSS for Windows. The effectiveness test will be performed using the intention-to-treat (ITT) principle and the per-protocol (PP) principle. Missing data will be adjusted with the last-observation-carried-forward (LOCF) imputation method. The safety test will be analyzed using the ITT principle, without adjustment. We will not perform interim analysis.

The student’s *t* test will be used for parametric variable comparisons between the two groups, and the paired *t* test will be used for intra-group comparisons. The Mann-Whitney *U* test will be used for non-parametric variable comparisons between the two groups, and the Wilcoxon signed-rank test will be used for intra-group comparisons.

The paired *t* test will be used to compare changes in MRI measurements, blood proteins, and cholesterol levels, before and after treatment. Correlation analysis will be used to estimate the relationship between the changes in MRI measures and changes in blood test results. Linear regression analysis will be used to compare changes in MRI measures, between the study group and the placebo group, using age and *APOE* genotype as covariates. Statistical significance will be set at *P* < 0.05, and all tests will be two-tailed.

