### Assessments

#### K-MMSE and SNSB

The K-MMSE will be performed at the screening visit and after 12 weeks of medication, to screen for MCI and assess the cognitive status of participants. This is a simple screening test for the longitudinal assessment of general cognition [10].

The full version of the SNSB-II will be measured at baseline and after 24 weeks of medication, to evaluate the effect of *Kami Guibi-tang* on cognitive function. The change in the mean of the SNSB scores, including the SNSB for dementia (SNSB-D) scores, will be compared between the KGT and placebo groups as a primary outcome.

The SNSB is one of the standardized neuropsychological test batteries, widely used in South Korea, for assessing general cognitive abilities. The test is composed of multiple subtests, which evaluate five cognitive aspects: attention, memory, language, visuospatial function, and executive function. Other related tests are included, such as the K-MMSE, Clinical Dementia Rating (CDR), Barthel–Activities of Daily Living (BADL), and Geriatric Depression Scale (GDS). The estimated completion time of the whole battery is 1.5–2 h [11].

A modified version of the original SNSB for dementia (SNSB-D) will be used to provide a general cognitive functioning (GCF) score, drawn from the sum of five domains. The maximum total score is 300 points consisting of 17/300 (6%) for attention, 27/300 (9%) for language and related function, 36/300 (12%) for visuospatial function, 150/300 (50%) for memory, and 70/300 (23%) for frontal/executive function [12]. The contents of the SNSB-D are shown in Table 2.

**Table 2 Tab2:** Contents of the Seoul Neuropsychological Battery for Dementia (SNSB-D)

Domains (total score)	Subtests	Maximum points
Attention (17)	Digit span forward	9
	Digit span backward	8
Language and related function (27)	K-BNT	15
	Calculation	12
Visuospatial function (36)	RCFT copy	36
Memory (150)	Orientation	6
	SVLT free/delayed recall	48
	SVLT recognition	12
	RCFT free/delayed recall	72
	RCFT recognition	12
Frontal/executive function (70)	Motor impersistence	3
	Contrasting program	3
	Go-no-go test	3
	Fist-edge-palm	3
	Luria loop	3
	Categoric word generation	20
	Phonemic word generation	15
	Stroop test-color reading	20
GCF score		300

*K-BNT* Korean short version of the Boston Naming Test, *RCFT* Rey Complex Figure Test, *SVLT* Seoul Verbal Learning Test, *GCF* global cognitive function

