#### MRI

Participants will undergo brain MRI at baseline and after 24 weeks of medication, to measure changes in brain metabolite and neurotransmitter levels, cerebral blood flow, tissue volume, and to evaluate brain abnormalities.

Proton magnetic resonance spectroscopy (^1^H-MRS) will be used to measure brain metabolite and neurotransmitter levels. Single-voxel Point-RESolved Spectroscopy (PRESS) MRS will be performed at the precuneus and posterior cingulate area of the brain, with a voxel size of 30 mm × 30 mm × 30 mm, to detect *N*-acetylaspartate (NAA) and glutamate-glutamine complex (Glx, with both Glu and Gln). *N*-acetylaspartate and Glx will be quantified using LCModel software. MEshcher-GArwood (MEGA) PRESS MRS will be performed to detect gamma-aminobutyric acid (GABA) in the same area as the PRESS MRS. The amount of GABA will be quantified using GANNET software. Pseudo-continuous arterial spin-labeling (pCASL) MRI will be performed to measure cerebral blood flow (CBF) in the brain. Voxel-based CBF will be mapped using local software. A three-dimensional T1-weighted image will be acquired using the magnetization-prepared rapid gradient-echo (MPRAGE) sequence, to quantify the gray and white matter tissue volume in the brain. T2-weighted turbo-spin echo (TSE), and fluid attenuation inversion recovery (FLAIR) sequences, will be used to evaluate brain abnormalities in participants. Changes in CBF and mean levels of NAA/Cr, Glx/Cr, and GABA/Cr, will be compared between KGT and placebo groups, as a primary outcome.

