#### Blood testing

Amyloid β protein, tau protein, HMGB, SERF 1A, and cholesterol derivatives will be measured in the blood at baseline and after 24 weeks of medication to observe changes in serum proteins and cholesterol associated with AD pathology. Changes in mean values of blood biomarker levels will be compared between the KGT and placebo groups.

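### LOCF on outcomes measured only at baseline and week 24 scores every missing week-24 value as zero change, which shrinks the effect and SD that this pilot should supply

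*Protocol article*

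**What the plan says.** The Data analyses section gives one rule for incomplete data: "Missing data will be adjusted with the last-observation-carried-forward (LOCF) imputation method". It also sets the analysis populations: "The effectiveness test will be performed using the intention-to-treat (ITT) principle and the per-protocol (PP) principle".

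The Assessments sections fix the measurement times:

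- SNSB (primary): "The full version of the SNSB-II will be measured at baseline and after 24 weeks of medication".
- MRI (primary): "Participants will undergo brain MRI at baseline and after 24 weeks of medication".
- Amyloid β, tau, HMGB, SERF 1A and cholesterol derivatives (secondary): "cholesterol derivatives will be measured in the blood at baseline and after 24 weeks of medication".

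The comparison is of change. For the SNSB: "The change in the mean of the SNSB scores, including the SNSB for dementia (SNSB-D) scores, will be compared between the KGT and placebo groups". The MRI and Blood testing sections likewise compare changes between the groups.

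Two measures have an intermediate value. For the cognitive screen, "The K-MMSE will be performed at the screening visit and after 12 weeks of medication", and the K-MMSE is also one of the related tests within the SNSB. Routine cholesterol is part of the week-12 safety laboratory panel (Safety assessment).

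The Sample size calculation section plans for 20% drop-out and gives sizing of a larger trial as one purpose of the pilot.

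**The concern.** LOCF presupposes at least one measurement after baseline. With two time points there is none, so for these outcomes the rule is baseline carried forward. Anyone in the ITT analysis without a week-24 value enters with a change of exactly zero, counted as if it had been observed.

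This is not a detail left to an analysis plan. The article states the method outright, and the method does not fit the article's own measurement schedule.

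Zeros pull each arm's mean change towards zero and usually narrow the spread of the changes. If the arms lose different proportions, the pull differs by arm and can produce a difference where none exists. A pilot is read mainly for its estimated effect and SD, and those are the two numbers that are distorted.

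**Working it through.** **Inputs from the protocol article.** Target 30, recruitment 38, drop-out 20% (Sample size calculation); 1:1 allocation (Randomization, allocation, blinding), so 19 per arm; two-sided 5% level (Data analyses). The stated recruitment figure reproduces: 30/(1 − 0.20) = 37.5, rounded up to 38. That leaves room for 8 of 38 (21%) without a week-24 value.

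**Assumptions.** The article gives no SD or expected change, so everything is in units of the SD of true change. In steps 1 to 3, drop-out is d = 0.20 in both arms, unrelated to outcome, and everyone who drops out lacks week-24 data.

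**1. Effect and SD.** With mean true change μ and SD 1:

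- LOCF mean = (1 − d)μ, so means and their difference are multiplied by 0.80. A true effect of 0.50 is estimated as 0.40.
- LOCF variance = (1 − d)(1 + dμ²).

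| Mean change μ (SD units) | LOCF SD / true SD |
|---|---|
| 0 | √0.80 = 0.894 |
| 0.25 | √(0.80 × 1.0125) = 0.900 |
| 0.5 | √(0.80 × 1.05) = 0.917 |
| 1.0 | √(0.80 × 1.20) = 0.980 |

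The SD is understated whenever |μ| < 1/√0.80 = 1.118. At μ = 0, the factor runs from 0.949 (d = 10%) to 0.837 (d = 30%). A simulation with 19 per arm and 4 zeros in each gave 0.887.

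**2. Significance test.** In simulation (40,000 trials, 19 per arm, effect 0.5), the LOCF estimate had a sampling SD of 0.292 and a mean reported SE of 0.291. The SE for the 15.2 per arm actually observed is √(2/15.2) = 0.363. Estimate and SE shrink together: 0.40/0.291 and 0.50/0.363 are both about 1.38. Type I error was 4.9% under LOCF and in completers; power was 25.9% and 26.3%. Confidence-interval coverage of the true effect did fall, to about 93.5% at effect 0.5 and 91% at 0.8, because the estimate is off-centre.

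**3. Sizing the later trial.** n per arm = 2(1.960 + 0.842)² × SD²/effect², for 80% power, at SD factor √0.80:

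| Assumed true effect | Correct n | LOCF SD, outside effect | LOCF SD and LOCF effect |
|---|---|---|---|
| 0.3 | 175 | 140 | 219 |
| 0.5 | 63 | 51 | 79 |
| 0.8 | 25 | 20 | 31 |

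- LOCF SD with an outside effect: the factor is 0.80 (0.81 at SD factor 0.90), so n is 19-20% too small and real power is about 71%.
- Both from LOCF: 0.80/0.80² = 1.25, so n is about 25% too large.
- If both arms change by 0.5 SD on average, the factors become 0.84 and 0.84/0.64 = 1.31.

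**4. Unequal drop-out (illustration).** Take 30% v 10%, no true effect and a common decline m. The LOCF difference is −0.70m + 0.90m = 0.20m in favour of the arm losing more people.

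- m = 0.2 SD gives 0.04 SD (coverage 94.8%).
- m = 0.5 SD gives 0.10 SD.
- The sign reverses if the split reverses or if both arms improve.

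**5. Outcome-related drop-out (hypothetical).** Keep 30% v 10%. Let completers decline 0.5 SD and drop-outs 1 SD more.

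- Truth: (−0.35 − 0.45) − (−0.45 − 0.15) = −0.20.
- LOCF: −0.35 + 0.45 = +0.10 (coverage about 82%).
- Observed data only: 0.00 (coverage about 92%).

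**The case against.** Several stronger readings are tempting, and the article does not support them.

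- **Standard errors too small, test invalid.** Step 2 shows that the SE is right for the LOCF estimator and that the test is practically unchanged under equal, random drop-out. The fault is a shrunken estimate.
- **The next trial will be underpowered.** That holds only if the LOCF SD is paired with an effect from elsewhere. With both inputs from LOCF, the next trial is too large.
- **The planning values must come from the LOCF data.** The article does not say so. The planned PP analysis would normally leave drop-outs out and so give changes without imputed zeros. This softens the point, but PP is limited to compliant completers and does not repair the ITT result.
- **Every drop-out and every marker is affected.** The Drop-out criteria include compliance below 80% and added cognitive medication. The text does not say whether such participants lack week-24 data, so 20% missing is an upper-end reading. The K-MMSE and routine cholesterol have week-12 values. Table 1 is not shown. If it schedules SNSB or MRI at early withdrawal, that value would be carried forward instead.
- **MCI is described as progressive, so zero change must flatter those who leave.** The Discussion uses that word of Alzheimer's disease. The Background calls MCI an intermediate phase and cites 16% of amnestic cases progressing to dementia per year, about 8% over 24 weeks at a constant rate. Outcome-related loss is plausible, but its size is unknown.
- **LOCF will turn harm into benefit.** Step 5 shows that this is possible, but the split and declines are assumed, and an analysis of observed data also misses the truth there.

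The mismatch between LOCF and a two-point schedule still stands.

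**Conclusion.** The point holds in a limited form. For the SNSB and SNSB-D, the MRI measures and the Alzheimer-related blood markers, the stated rule is baseline carried forward in the ITT analysis. At the article's own 20% drop-out, taken as all missing at week 24, equal by arm and unrelated to outcome, the difference falls to 0.80 of its value and the SD to 0.89-0.92 for mean changes of 0 to 0.5 SD. Less missing data means proportionately less attenuation.

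The effect on the later trial's size can go either way, so it should not be described simply as loss of power. The spurious differences of 0.04 to 0.10 SD under unequal drop-out are illustrations, as the article gives no split or expected decline.

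The severity is should-fix. The trial is exploratory and a PP analysis is also planned, but the rule affects the primary outcomes and the numbers the pilot is meant to hand on.

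**What to change.** Before unblinding, replace the LOCF sentence for these outcomes with the following:

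1. **Main ITT analysis.** Baseline-adjusted regression (ANCOVA) of observed week-24 values by randomized arm, with week-24 data collected where possible from participants who stop treatment. Alternatively, use multiple imputation with a small predictor set: baseline value, arm and age. Imputing separately by arm from many predictors would be fragile with about 15 observed per arm. The week-12 K-MMSE adds little, since entry requires a normal score and the Discussion itself notes ceiling effects.
2. **One sensitivity analysis** in which participants with missing week-24 values are assumed to decline more than completers, over a stated range. It is needed because the main analysis does not remove bias from outcome-related drop-out.
3. **Planning values.** Estimate the SD of change and the effect for the larger trial from observed changes only, and report the number observed per arm.

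The cost is a few sentences, a little more programming and a somewhat wider confidence interval. No new measurement is required; following up participants who stop treatment takes some site effort where it is not already done.

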## Background

Mild cognitive impairment (MCI) is an intermediate phase between normal aging and dementia. This clinical condition is characterized by self or caregiver-reported memory or cognitive complaints, and objective cognitive impairment, that is not severe enough to interfere with daily activities [1]. The majority of people with MCI develop dementia due to Alzheimer’s disease (AD) [2]. In particular, the amnestic subtype of MCI, which manifests as memory complaints, is often caused by degenerative etiologies and is generally regarded as a precursor of AD. A previous study revealed that 16% of amnestic MCI (aMCI) patients progress to dementia each year, 99% of whom receive an AD diagnosis [3]. Early treatment of mild-to-moderate AD is associated with better responses than later treatment, so treatment of MCI may delay progression to AD [4]. There is, however, no treatment approved for enhancing *memory function, or preventing further cognitive decline in MCI* [5]*.*

*Kami Guibi-tang* (KGT) is a popular herbal medicine used in Korean and Kampo medicine to treat amnesia, insomnia, loss of appetite, and depression. Several studies have explored the effects of KGT on cognitive impairment, particularly in AD. KGT improved learning performance in a mouse model of accelerated senescence [6], and reduced spatial memory impairment induced by scopolamine or delta-tetrahydrocannabinol [7]. In the 5XFAD mouse model of AD, KGT improved deficits in object recognition memory, and reversed the degeneration of cortical axons and presynaptic terminals [8]. A clinical study demonstrated that the Mini-Mental State Examination (MMSE) score of AD patients improved after receiving orally administered KGT extract granules for 3 months [9].

Previous studies have suggested that KGT could be beneficial for cognitive function in AD patients. However, few clinical trials have been published, and no study has yet investigated the effect of KGT on MCI. This pilot study aims to determine the effectiveness and safety of KGT for improving cognitive function, the influence on neuroimaging and neurochemical biomarkers, and the potential therapeutic effects in MCI.

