### Randomization, allocation, blinding

A researcher uninvolved in the assessment will generate a random sequence using SPSS ver. 18. We will randomly allocate participants to either the treatment or the control group, in a 1:1 ratio using the block randomization method, with a block size of 4. The participants, assessor, clinical trial pharmacist, and researchers will be blinded to the allocations throughout the course of the study. Cases will be unblinded only if serious adverse events (SAE) occur.

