### Intervention

After randomization, the treatment group will receive KGT granules (3 g/pack) and the control group will receive placebo granules (3 g/pack). *Kami Guibi-tang*, the herbal medicine under study, is composed of 14 drugs: *Astragali Radix* (1.0 g), *Ginseng Radix* (1.0 g), *Atractylodis Rhizoma* (1.0 g), *Poria cocos* (1.0 g), *Zizyphi Fructus* (0.67 g), *Zingiberis Rhizoma* (0.33 g), *Saussureae Radix* (0.33 g), *Glycyrrhizae Radix* (0.33 g), *Zizyphi Spinosi Semen* (1.0 g), *Longan Arillus* (1.0 g), *Angelicae Radix* (0.67 g), *Polygalae Radix* (0.67 g), *Bupleuri Radix* (1.0 g), *Moutan Radicis Cortex* (0.67 g), and *Gardeniae Fructus* (0.67 g). Treatment granules will be manufactured by Kyoung Bang Pharmaceutical Co., Ltd. (Incheon, Korea), which has been certified for Good Manufacturing Practice.

Placebo granules will be produced by the same manufacturer, using the standard method of placebo manufacturing according to the Korean Good Manufacturing Practice guidelines. The placebo will be similar to the *Kami Guibi-tang* granules in appearance, taste, and smell.

An independent clinical pharmacist will distribute KGT or placebo granules to the study participants. The pharmacist will instruct participants to dissolve the granules in hot water, stir well, and drink the solution three times per day, 30 min after meals, for 24 consecutive weeks. The researchers will call participants by phone once a week, reminding them to comply with the medication schedule.

The administration of medicine for underlying diseases, such as hypertension or diabetes mellitus, will be permitted during the intervention; however, any medication that can affect cognitive function will be prohibited. We will ask the participants to report all medications taken during the study at each visit, and record the names, duration, and dosage of the drugs on the case report form (CRF).

Participants will be required to return the unused trial drugs at the next visit. The number of returned drugs will be assessed to evaluate drug compliance, and participants with less than 80% compliance will be excluded.

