### Outcome

Primary outcomes will include changes in cognitive function, and changes in imaging biomarkers, before and after taking KGT or placebo granules. For assessing cognitive function, the SNSB will be conducted and changes in SNSB results will be analyzed. For measuring the imaging biomarkers, brain MRI scans will be taken to assess the levels of brain metabolites, neurotransmitters, and cerebral blood flow (CBF).

Secondary outcomes will include the safety of KGT granules, and changes in blood-based biomarkers including proteins (amyloid β (Aβ) and tau) and cholesterols, and a comparison of MRI changes between the two groups using age and genotype as covariates. For safety assessments, blood chemistry tests for AST/ALT, glucose, blood urea nitrogen (BUN), Cr, Na, K, Cl, lactate dehydrogenase (LDH), creatine phosphokinase (CPK), and an electrocardiogram (ECG) will be conducted. Blood biomarkers including Aβ protein, tau protein, high-mobility group box (HMGB), small EDRK-rich factor (SERF) 1A, and cholesterol derivatives will also be measured. *APOE* genotype testing will be performed. Detailed explanations are shown below.

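### Safety is fixed on the ITT principle instead of on exposure, which can slightly dilute an excess of harms; an at-least-one-dose, as-received safety set is a cheap improvement

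*Protocol article*

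**What the plan says.** The Data analyses section sets the populations in two steps. For effectiveness, "The effectiveness test will be performed using the intention-to-treat (ITT) principle and the per-protocol (PP) principle", with last observation carried forward for missing values. For safety, "The safety test will be analyzed using the ITT principle, without adjustment". No other section defines a safety set based on taking at least one dose, and none says that safety data are grouped by the product received.

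Safety is part of the stated purpose. The Background section says "This pilot study aims to determine the effectiveness and safety of KGT for improving cognitive function". In the outcome hierarchy it ranks lower: "Secondary outcomes will include the safety of KGT granules" (Outcome section).

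The Drop-out criteria and the Intervention section remove participants whose compliance falls below 80%. Neither they nor the Data analyses section says how that removal fits with an ITT safety analysis.

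**The concern.** ITT suits an effectiveness comparison: it preserves the randomised groups, and the dilution it brings usually works against claiming a benefit. For harms, the same dilution works in favour of claiming safety. Two routes lead there:

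1. A participant randomised to KGT who never takes a dose adds to the KGT denominator but cannot have a KGT-related event.
2. A participant randomised to placebo who is handed KGT, or the reverse, has any event credited to the wrong product.

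In a trial of this size one person is a visible fraction of an arm. The Discussion section expects the study to supply evidence on safety and to support a larger confirmatory trial, so adverse-event proportions that lean towards no difference would be carried forward.

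**Working it through.** **Inputs from the article.** Sample size calculation section: "Our target sample size is 30, so 38 individuals will be recruited to allow for a 20% dropout rate". Randomization section: allocation "in a 1:1 ratio using the block randomization method, with a block size of 4".

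**The article's own figure.** 30/(1 − 0.20) = 37.5, rounded up to 38, which agrees with the stated number. At 1:1 this is 38/2 = 19 per arm, and one person is 1/19 = 5.3% of an arm.

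**Assumed inputs.** The article gives no adverse-event rates, no number never dosed and no number given the wrong granules. I used KGT and placebo event rates of 20%/5%, 30%/10% and 40%/10%, with 1, 2 or 4 of 19 KGT participants never dosed, or 1 or 2 kit swaps each way. Four is an extreme: the planned dropout is 38 − 30 = 8, or 4 per arm, so all of the KGT arm's dropouts would have to leave before the first dose.

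**Never dosed.** Let p1 and p0 be the KGT and placebo event rates, and u the number of KGT participants never dosed, each at the background rate p0. The KGT rate by randomised arm is [(19 − u)·p1 + u·p0]/19, so the risk difference is (p1 − p0)·(1 − u/19).

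**Two-way swap.** With s participants swapped in each direction, the difference by randomised arm is (p1 − p0)·(1 − 2s/19).

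| Assumed rates | True difference | u = 1 | u = 2 or s = 1 | u = 4 or s = 2 |
|---|---|---|---|---|
| 20% v 5% | 15.0 | 14.2 | 13.4 | 11.8 |
| 30% v 10% | 20.0 | 18.9 | 17.9 | 15.8 |
| 40% v 10% | 30.0 | 28.4 | 26.8 | 23.7 |
| Share of excess lost | 0 | 5.3% | 10.5% | 21.1% |

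Differences are in percentage points.

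**One-way mis-dispensing, counts assumed.** One participant randomised to placebo takes KGT and has an event. By granules taken: 7/20 = 35.0% v 5/18 = 27.8%, a difference of 7.2 points. By randomised arm: 6/19 v 6/19, a difference of 0. This is one realised outcome. On average, one such placebo-to-KGT error costs 1/19 of the excess, for example 20.0 to 18.9 points.

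**Direction for a single never-dosed person, counts assumed.** Suppose the person is in the placebo arm and has no event. Excluding them gives 6/19 = 31.6% v 5/18 = 27.8%, or 3.8 points. Including them gives 6/19 v 5/19 = 26.3%, or 5.3 points. Here ITT widens the difference.

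**The case against.** The strongest reply is that the sentence is condensed. It follows directly on a plan for ITT, per-protocol and imputed analyses of effectiveness, so it may only mean that safety has no per-protocol restriction and no imputation. The article does not define ITT in detail, and set definitions are often left to a fuller document. That reading is plausible. But the text names a rule for safety, and taken as written the rule keeps never-dosed participants and groups everyone by randomised arm. One sentence would settle which is meant.

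ITT also has a real merit here: it keeps low-compliance and withdrawn participants, whom the compliance rule would otherwise remove. This stands, but a set requiring only one dose keeps them too.

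The harm is also conditional. Granules are handed out by an independent pharmacist at a single centre, with weekly compliance calls, and nothing in the article points to undosed participants or dispensing errors. This stands in full and limits the weight of the point.

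A reader might infer three stronger things that the article does not support:

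- That every never-dosed participant pulls the arms together. The last calculation above shows otherwise.
- That changes in laboratory values are diluted in the same way. If a never-dosed participant has no post-baseline sample, and if no adjustment means no imputation, that person does not enter the change comparison. The issue is mainly about adverse-event proportions.
- That a primary objective is compromised. Safety is in the stated aim but is formally a secondary outcome of a pilot.

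**Conclusion.** The point holds as a minor one. The article fixes a safety population that is less suitable than the usual exposure-based set, and on average the departure favours an appearance of safety. The size is 5.3% of the excess risk per never-dosed KGT participant and 10.5% per two-way swap. This rests on 19 per arm and on never-dosed participants having the background event rate; the event rates and counts used for illustration are assumptions. If all participants took the granules assigned to them, the two analyses coincide and the effect is zero. The article does not allow the conclusion that the trial's safety results will in fact be biased.

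**What to change.** Replace the safety sentence with one that states: safety is analysed in all randomised participants who took at least one dose of trial granules, including those with low compliance and those who withdrew, grouped by the granules actually received, without imputation; the analysis by randomised arm is kept as a check.

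Exposure can largely be read from what the plan already collects: "The number of returned drugs will be assessed to evaluate drug compliance" (Intervention section). Those counts show how much was taken, not which product. Grouping by product therefore needs the allocation list, compared with what the pharmacist handed to each participant. The article does not describe a dispensing log, so the sponsor should confirm that this comparison can be made.

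The cost is one sentence and one additional analysis set. Sample size, visits and blinding are unchanged.

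### The between-group analyses of change leave out the outcome's own baseline value as a covariate, although it is measured for every primary outcome

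*Protocol article*

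**What the plan says.** All references are to the protocol article.

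- **SNSB.** Under K-MMSE and SNSB: "The change in the mean of the SNSB scores, including the SNSB for dementia (SNSB-D) scores, will be compared between the KGT and placebo groups". On timing: "The full version of the SNSB-II will be measured at baseline and after 24 weeks of medication".
- **MRI.** Under MRI: "Changes in CBF and mean levels of NAA/Cr, Glx/Cr, and GABA/Cr, will be compared between KGT and placebo groups, as a primary outcome". Scans are taken at baseline and week 24.
- **Tests.** Under Data analyses, Student's t test "will be used for parametric variable comparisons between the two groups", and Mann-Whitney takes its place for non-parametric variables. The same section adds: "Linear regression analysis will be used to compare changes in MRI measures, between the study group and the placebo group". The covariates listed for that regression are age and APOE genotype.
- **Status of the adjusted MRI comparison.** The Outcome section places "a comparison of MRI changes between the two groups using age and genotype as covariates" among the secondary outcomes.

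The t-test sentence names neither SNSB nor MRI. That it governs their primary between-group comparisons is an inference, because no other between-group test is given for SNSB and the MRI regression is secondary. No described model contains the outcome's baseline value as a covariate.

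**The concern.** A t test on change is a regression in which the baseline slope is set to 1 rather than estimated. When the correlation between baseline and week 24 is below 1, that slope is too steep. The baseline is then over-subtracted, and this has two consequences.

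- The estimate is noisier than it need be.
- If one arm happens to start higher, regression to the mean carries part of that difference into the estimated treatment effect.

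Both matter more in a small trial. The article describes 1:1 blocks of 4 and no stratification, so nothing described limits chance imbalance in baseline SNSB or MRI values. The pilot is also meant to supply figures for sizing a larger trial. A baseline-adjusted effect and its residual SD would serve that purpose better than a t test on change.

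**Working it through.** **Inputs from the article.** The target is 30, recruitment is 38 and dropout is 20% (Sample size calculation). Allocation is 1:1 in blocks of 4 (Randomization, allocation, blinding). Tests are two-sided at 0.05 (Data analyses). The stated 38 reproduces: 30 / 0.8 = 37.5, rounded up to 38. This gives 15 completers or 19 recruited per arm. The article states no SD, effect size or power.

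**Assumptions.** rho, the within-arm correlation between baseline and week 24, is taken from 0.5 to 0.9. SDs are equal at the two times.

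**Precision**

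- Variance of a change: 2(1 - rho) SD².
- Residual variance with baseline as covariate: (1 - rho²) SD².
- Large-sample ratio: (1 + rho)/2.
- Penalty for estimating the slope: (N - 3)/(N - 4) = 27/26 = 1.038 at N = 30.

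For example, at rho = 0.5 the ratio is 0.75 × 1.038 = 0.78, and 15 / 0.779 = 19.3 patients per arm on the change-score scale.

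Results at 15 per arm (detectable difference at 80% power, in SD units):

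| rho | Variance ratio, ANCOVA / change | Equivalent n per arm | Detectable difference, change → ANCOVA |
|---|---|---|---|
| 0.5 | 0.78 | 19.3 | 1.06 → 0.94 |
| 0.7 | 0.88 | 17.0 | 0.82 → 0.77 |
| 0.8 | 0.94 | 16.0 | 0.67 → 0.65 |
| 0.9 | 0.99 | 15.2 | 0.474 → 0.471 |

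At 19 per arm the penalty is 35/34 and the ratios are 0.77, 0.88, 0.93 and 0.98.

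**Chance imbalance**

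- SD of the baseline difference between arms: sqrt(2/15) = 0.37 SD, or sqrt(2/19) = 0.32 SD.
- Probability that it exceeds 0.5 SD in either direction: 17% at 15 per arm, 12% at 19.
- Given a baseline difference D, the change-score contrast is off by -(1 - rho)D. For D = 0.5 SD the size is 0.25, 0.15, 0.10 and 0.05 SD at rho 0.5, 0.7, 0.8 and 0.9.

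**Simulation** (20,000 trials per rho, 15 per arm)

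- Overall type I error of the change-score test: 4.7% to 5.1%.
- Type I error in trials with an imbalance above 0.5 SD: 11.7%, 8.9%, 7.4% and 5.6% at rho 0.5, 0.7, 0.8 and 0.9, against 4.7% to 5.5% with ANCOVA.
- Power for a true 0.8 SD difference, change score against ANCOVA: 56% and 67% (rho 0.5), 78% and 82% (0.7), 91% and 93% (0.8), 99.7% for both (0.9).

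**Scope.** These figures compare an unadjusted t test on change with ANCOVA on baseline alone. The gain from adding baseline to the age and APOE regression also depends on how much of the change those two covariates already explain, which the article does not allow one to compute.

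**The case against.** Several points on the other side stand.

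- A reader might infer that the tests ignore baseline, or that imbalance goes uncorrected. The article does not support that: the compared quantity is change, which subtracts baseline. The fault is over-correction, with a remainder of (1 - rho) times the imbalance.
- A reader might infer that the planned test is invalid. It is not. Over randomization it is unbiased and holds its type I error. The loss is in efficiency and in conditional bias.
- A reader might take (1 + rho)/2 at face value and claim 33%, 18% or 11% more participants free of charge at rho 0.5, 0.7 and 0.8. That formula is a large-sample one. With the slope penalty at N = 30 the gains are about 28%, 13% and 7%, and about 1% at rho 0.9.
- A reader might say that the unadjusted and adjusted MRI comparisons give two answers to one primary question. The Outcome section lists the adjusted one as secondary, so the order is stated.
- Adding covariates has a price. With two covariates the penalty is (N - 3)/(N - 5) = 27/25 = 1.08. If the second adds nothing, the ratio at rho 0.9 is 0.95 × 1.08 = 1.03, a small loss. The case for baseline is therefore no case for moving age or APOE into the primary analysis.
- Last-observation-carried-forward sets week 24 equal to baseline for dropouts, which raises rho in the intention-to-treat set. If 8 of 38 are carried forward and are otherwise like the rest, rho 0.5 becomes (30 × 0.5 + 8)/38 = 0.61. The ratio at 19 per arm then moves from 0.77 to (1.61/2) × 35/34 = 0.83.
- Some SNSB-D subtests have a maximum of 3 points (Table 2), where a linear model is doubtful.

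It is also fair to say that this is a pilot without a power calculation, so no stated figure is overturned. That limits the weight of the point but does not remove it: the test and the MRI covariates are named in the article, and the missing covariate is already collected.

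**Conclusion.** The point holds as a matter of efficiency and conditional bias, not validity. The outcome's baseline value is measured for every primary outcome and enters no described between-group model. Including it would reduce the variance at 15 per arm by about 22% at rho 0.5, 12% at 0.7, 6% at 0.8 and 1% at 0.9. It would also remove a conditional bias of 0.25 to 0.05 SD over the same range in a trial with a 0.5 SD baseline imbalance.

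The size rests on rho, which the article does not give, on equal SDs at both times, and on reading the general t-test sentence as covering the primary outcomes. The change is worth making because it uses data already planned and, over the range examined, adjustment for baseline alone was never less precise than the change score.

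**What to change.** - For the continuous primary outcomes (SNSB-D/GCF score, NAA/Cr, Glx/Cr, GABA/Cr and CBF), make the primary between-group comparison an ANCOVA of the week-24 value, or equivalently the change, on treatment plus the baseline value of that outcome. Report the adjusted difference with its 95% CI.
- Add the baseline MRI value to the existing secondary regression, beside age and APOE genotype. Leave those two covariates in the secondary analysis.
- Keep a rank-based test for clearly non-normal outcomes and short-range subtests.

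The cost is a change of analysis wording and one degree of freedom per model, with no new data or visits. If rho proves to be near 0.9, almost nothing is gained. The change should be fixed and dated before unblinding. The article plans a double-blind trial with no interim analysis, so the wording can be settled without sight of results by arm.
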